### Preparation and application of tissue engineered materials

Autologous BM-MSCs are cultivated from the iliac crest bone marrow aspirate for about 6 to 8 weeks as per previously reported methods [10, 13–19]. Before incubation of BM-MSCs, the adequate quantity of serum is prepared by dividing the blood samples several times. Moreover, the patient’s own PRP is prepared on the day before the application of tissue engineered materials. The other components of the tissue engineered materials, thrombin (Thrombin oral/topical 5000 units “JB” or Thrombin oral fine gran. 5000 units), calcium (Calcium Chloride “Yamazen”), and β-TCP (OSferion) are purchased from Japan Blood Products Organization (Tokyo, Japan), Yamazen Corporation (Osaka, Japan), and Olympus Corporation (Tokyo, Japan), respectively.

A 10% Calcium chloride solution is prepared in advance, and thrombin (5000 units) is dissolved in 5 mL of the 10% calcium chloride solution. The mixture of BM-MSCs (about 1 × 10^7^ cells) and PRP (2.0 mL per 3.0 mL defect) is combined with the thrombin solution (0.5 mL per 3.0 mL defect). After the contents start to have a gel-like appearance, they are mixed with β-TCP (0.5 g per 3.0 mL defect). The appearance of the mixture of BM-MSCs, PRP, thrombin, calcium, and β-TCP is shown in Fig. 2. BM-MSCs are not included in this mixture for the control group. Next, the mixture is injected to the bone augmentation site following applied operation such as guided bone regeneration, or sinus floor elevation after meticulous debridement.

**Fig. 2 Fig2:**
[figure not shown]
The appearance of the mixture of BM-MSCs, PRP, thrombin, calcium, and β-TCP. The mixture of BM-MSCs and PRP is combined with the thrombin-calcium solution, and then these contents start to have a gel-like appearance. After that, they are mixed with β-TCP

Incidentally, Bisphosphonate and denosumabu are prohibited during the trial in order to modify bone metabolism and have the risk of osteonecrosis of the jaw.

### Response variables (outcomes)

Patients will be followed-up for 24 months after transplantation of materials. The TEOM study schedule is shown in Table 1. All data are collected via an electronic data capture system (Viedoc™, PCG Solutions Ab. Uppsala, Sweden), and checked by data manager and monitor according to the data management and monitoring plan.

**Table 1 Tab1:** The TEOM study data collection schedule

	Screening	Preparation for operation				Operation	Observation period					
	Registration and assignment	† Blood sampling	† Bone marrow sampling	Preoperative examination	Day − 1	Day 0	Day 1	Month 1	Month 3	Month 6	Month 12	Month 24
Eligibility criteria	X											
Vital signs^‡^		X		X		X	X	X				
Laboratory tests												
Infections^§^, HbA1c	X											
Hematology^¶^, Biochemistry^††^, CRP, Coagulation^‡‡^	X	X^§§^		X			X	X	X	X	X	X
Urinalysis^¶¶^				X			X	X	X	X	X	X
Blood sampling		X			X							
Bone marrow sampling			X									
Panoramic X-ray	X						X	X	X	X	X	X
Facial CT	X						X	X	X	X	X	X
Tooth mobility^†††^	X								X	X	X	X
Masticatory force	X							X	X	X	X	X
Biopsy of bone (if needed) for histology								X	X	X	X	X
Transplantation of tissue engineered materials						X						
Concomitant therapies	X	X	X	X	X	X	X	X	X	X	X	X
Adverse events		X	X	X	X	X	X	X	X	X	X	X

† Only BM-MSCs group

‡ Blood pressure, pulse rate, body temperature

§ HBs antigen, HCV antibody, HIV antibody, HTLV-1 antibody, serologic test for syphilis, PVB19 antibody

¶ Red blood cell count, hemoglobin, hematocrit, white blood cell count, fraction of leucocytes (basophil, eosinophil, neutrophil, lymphocyte, monocyte), platelet count

†† Total protein, albumin, total cholesterol, blood urea nitrogen, creatinine, uric acid, sodium, chloride, potassium, calcium, phosphate, lactate dehydrogenase, aspartate aminotransferase, alanine aminotransferase, alkaline phosphatase, gamma-glutamyl transferase, total bilirubin

‡‡ Prothrombin time, activated partial thromboplastin time, fibrinogen

§§ Only red blood cell count, hemoglobin, white blood cell count, platelet count

¶¶ pH, protein, glucose, urobilinogen, occult blood

††† After setting of dental implant

Abbreviations: CRP, C-reactive protein; CT, Computed Tomography

As a general rule, the primary endpoint should reflect clinically relevant and meaningful effects [21]; therefore, we selected the rate of implanted sites with successful bone augmentation as the primary endpoint of the TEOM study. The definition of successful bone regeneration is the consideration as to whether the strength of augmented bone site is able to place a dental implant or not.

The secondary endpoints are as follows:Regenerated bone height by facial CT and panoramic X-ray imagePercentage of the regenerated bone height over the height of the initial defect by facial CT and panoramic X-ray imageCT valueRate of successful implant placementTime from transplantation to implant placementSurvival rate and time of dental implantTooth mobility by the implant stability meters from Osstell (SASAKI Co., Ltd. Aich, Japan)Masticatory force by Occlusal Force-Meter (GM10, Nagano Keiki. Tokyo, Japan)Histological assessmentAdverse eventLaboratory tests

In addition to achievement of the primary endpoint criteria, the clinical meaning of additional BM-MSCs in bone augmentation will be considered comprehensively according to these secondary endpoint results.

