## Methods/design

### Overall design and objective

The primary objective of this clinical study is to evaluate the efficacy and safety of bone regeneration therapy using tissue engineering materials including BM-MSCs in patients with maxillomandibular bone defects resulting from maxillofacial injury, or tumor/cyst removal. The TEOM study is an open-label, single-center (Nagoya University Hospital, Japan), randomized controlled study involving a total of 83 regions (BM-MSCs group: control group = 55 regions: 28 regions) by the Fédération Dentaire Internationale numbering system in patients with large jawbone defects. Maximum patient number is 29 (BM-MSCs group: control group = 19 patients: 10 patients) with at least 3 defect segments per patient thereof. A flow diagram of the TEOM study is shown in Fig. 1. The primary endpoint of this study is the rate of procedure sites with successful bone regeneration that satisfies both of the following definitions; i) CT value is at least 400, and ii) Bone height is over 10 mm. We decided as a specific hypothesis that the rate of patients who fulfil the primary endpoint criteria is similar in both groups, and the non-inferiority margin is 15.0%. Additionally, we will consider whether or not secondary endpoints in the BM-MSCs group will be superior to those in the control group.

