### Registration and informed consent

Patients are registered as candidates for this study after providing a written informed consent form. After the investigators have confirmed that they meet all eligibility criteria, the patients are enrolled via an electronic data capture system (Viedoc™, PCG Solutions Ab. Uppsala, Sweden), with subsequent randomized assignment to either the BM-MSCs group or control group by the minimization method. Allocation factors are shown as follows: i) the number of regeneration segments (< 4 segments, 5 to 6 segments, > 7 segments), ii) the method of applied operation (sinus floor elevation, any other method of operation, sinus floor elevation with any other method of operation), bone regeneration site (maxilla, mandibular, both).

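### Table 1 schedules adverse-event collection after randomisation at two visits that only the BM-MSCs arm has, so the safety comparison rests on windows of unequal length

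*Protocol article*

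**What the plan says.** Under Registration and informed consent, patients are enrolled "with subsequent randomized assignment to either the BM-MSCs group or control group by the minimization method". The first column of Table 1 (Response variables) is headed "Registration and assignment", so randomisation comes before any sampling. That column has a mark for concomitant therapies but none for adverse events.

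The next two columns, blood sampling and bone marrow sampling, are limited by footnote to one arm: "Only BM-MSCs group". Both have an adverse-event mark. The first adverse-event mark in a column common to both arms is at "Preoperative examination", and the article does not say how long before surgery that visit falls.

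Under Preparation and application of tissue engineered materials: "Autologous BM-MSCs are cultivated from the iliac crest bone marrow aspirate for about 6 to 8 weeks". Before incubation, "the adequate quantity of serum is prepared by dividing the blood samples several times"; no duration is given. The end of observation is tied to surgery: "Patients will be followed-up for 24 months after transplantation of materials".

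Safety belongs to the primary objective, which is "to evaluate the efficacy and safety of bone regeneration therapy using tissue engineering materials". The Background presents it as a comparison of the two mixtures, and adverse events are a listed secondary endpoint.

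**The concern.** Both arms leave the same randomisation point and stop at the same distance from surgery, but scheduled adverse-event collection begins at different places. The cell arm has two extra collection visits, separated from surgery by the culture period.

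Events caused by aspiration and blood drawing are rightly counted against the cell strategy. An unrelated event in the same weeks, however, has scheduled visits at which to be recorded in one arm only. A comparison of adverse events by arm would then mix three things: any effect of the cells, the burden of harvest, and a longer time in which to record events. The monitoring committee also reads the safety data, and a difference in lead-in weighs more while follow-up is short.

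**Working it through.** No figure in the article depends on this point, so there is none to reproduce. The check is a reading of Table 1 by arm, followed by arithmetic on window lengths.

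**Adverse-event marks by arm**

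| Column of Table 1 | BM-MSCs | Control |
|---|---|---|
| Registration and assignment | no mark | no mark |
| Blood sampling | mark | visit not held |
| Bone marrow sampling | mark | visit not held |
| Preoperative examination and all later columns | mark | mark |

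**Inputs**
- Follow-up after transplantation: 24 months = 24 × 365.25 / 12 / 7 = 104.4 weeks (Response variables).
- Culture time C: 6 to 8 weeks (Preparation and application).
- Serum-collection time before incubation: positive, not stated, left out of the sums.
- L, the lead of the control preoperative examination over surgery: not stated, so varied from 0 to 8 weeks.

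**Window lengths**
- BM-MSCs = 104.4 + C = 110.4 to 112.4 weeks, plus serum collection.
- Control = 104.4 + L.
- Excess = C − L weeks. Relative excess = (104.4 + C) / (104.4 + L) − 1.

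| L (weeks) | Excess, C = 6 | Excess, C = 8 |
|---|---|---|
| 0 | 6 weeks (5.7%) | 8 weeks (7.7%) |
| 2 | 4 weeks (3.8%) | 6 weeks (5.6%) |
| 4 | 2 weeks (1.8%) | 4 weeks (3.7%) |
| 6 | 0 | 2 weeks (1.8%) |
| 8 | −2 weeks (−1.8%) | 0 |

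**What this does to a risk.** Assume a constant hazard, no true difference, L = 0, and a 30% risk of any adverse event in control (the 30% is illustrative). The BM-MSCs arm would show 1 − 0.70^(110.4/104.4) = 31.4% to 1 − 0.70^(112.4/104.4) = 31.9%, an inflation of 1.4 to 1.9 percentage points.

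**Against sampling error.** With the planned maximum of 19 and 10 patients (Overall design and objective), the standard error of the risk difference at 30% is √(0.3 × 0.7 × (1/19 + 1/10)) = 0.18, or 18 points. The bias is about one tenth of that.

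**Early looks.** With Month 1 taken as 4.35 weeks after surgery, the ratio of windows up to Month 1 is (6 + 4.35)/4.35 = 2.4 to (8 + 4.35)/4.35 = 2.8 at L = 0. At L = 2 it is 10.35/6.35 = 1.6 to 12.35/6.35 = 1.9.

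**The case against.** The strongest reply is that a mark in a collection schedule shows when events are asked about, not the interval covered. The Month 12 mark presumably covers the time since Month 6. In the same way, the control mark at the preoperative examination could cover the time since assignment. A reader might infer from Table 1 that control patients go unobserved after randomisation; the article does not say that, and the full protocol may define the reporting period. This part of the objection stands. Even so, it does not equalise the windows: L is simply replaced by the control patient's wait from assignment to surgery, and the cell arm still has the longer period before surgery unless controls wait equally long.

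Two other strong readings also fail. One is that recording opens weeks earlier after randomisation in the cell arm. The article times neither sampling nor the control visits from assignment, so the lead is established only relative to Day 0. The other is that the excess is at least 6 to 8 weeks. On culture time alone that is the figure at L = 0, and it shrinks as L grows.

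It is also fair to say that the article commits to no crude any-event comparison. Its Statistical analysis section gives descriptive summaries and refers to an analysis plan, which could split dated events at Day 0. That plan could not, however, recover control events that were not collected.

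Finally, a comparison from Day 0 alone would take harvest harms out of the contrast and condition on reaching transplantation, which sits badly with the stated intention-to-treat principle. That is right, and the total from assignment should be kept.

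**Conclusion.** The point holds as an imbalance in the scheduled adverse-event windows. On culture time alone, the BM-MSCs window is longer by up to about 6-8 weeks, about 6-8% of 24 months, less L; serum collection adds an amount the article does not state. The imbalance runs in one direction, towards more recorded events in the cell arm, provided the control preoperative examination falls closer to surgery than the culture time. Nothing in the article indicates otherwise, but it does not state the timing.

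Over the full follow-up the effect is small, well inside the sampling error of a trial of at most 29 patients, and it does not touch the primary endpoint. It is relatively larger in early safety summaries. The translation into risks rests on a constant hazard and an assumed 30% control risk. The case for acting is that the correction costs almost nothing, and missing control events cannot be supplied at the analysis stage.

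**What to change.** - Mark adverse-event recording from assignment in both arms of Table 1. Ask control patients, at the existing preoperative examination, about the whole time since assignment.
- Date every event, and tabulate by arm for two periods: assignment to Day 0, where harvest harms will show, and Day 0 to Month 24.
- Keep the total from assignment, with person-time for each arm, as the intention-to-treat summary, because the wait before surgery may still differ between arms.
- Give the monitoring committee the same split.

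The cost is one mark in the schedule, one line on the case report form and split tables. No visit is added. For patients already enrolled, events between assignment and the preoperative examination would have to be sought retrospectively, and should be labelled as such.

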### Data and safety monitoring committee

An independent data and safety monitoring committee is established in this study for assessment of the safety data in order to decide whether to continue, modify, or stop a trial, and performed according to the standard operating procedure.

### Sample size calculation

We assume that the rates of ‘Successful bone regeneration’ as a primary endpoint are commonly 95% in the two groups based on our clinical pilot study [14]. The non-inferiority margin is set to be 15.0% as a clinically acceptable difference.

With 83 sites per group, there was 80% power to examine the non-inferiority of the BM-MSCs group relative to the control group under the assumption of a two-sided significance level of 5.0% and an allocation ratio of 2: 1 to the BM-MSCs group or control group.

### Statistical analysis

All the analysis is based on an intention to treat principle. The primary analysis is to estimate the differences in the rate of ‘Successful bone regeneration’ and its 95% confidence interval (CI) based on the Clopper-Pearson method. The non-inferiority of the BM-MSCs group relative to the control group is evaluated based on whether the lower limit of the 95% CI exceeds the non-inferiority margin of 15%. The descriptive statistics for continuous variables and frequency and proportion for categorical variables are calculated. The time-to-event data are summarized by using the Kaplan-Meier method. All the statistical tests use a two-sided *p*-value. *P* < 0.05 is considered to be statistically significant. All the statistical analyses are performed by using the SAS version 9.4 (SAS Institute, Inc., Cary, NC, USA), and performed according to the statistical analysis plan.

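### Every analysis of a non-inferiority trial rests on intention to treat alone, although BM-MSCs patients may never receive cells; the bias could run either way, and no named analysis would show which

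*Protocol article*

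**What the plan says.** The article's Statistical analysis section opens: "All the analysis is based on an intention to treat principle". The same paragraph sets the primary decision: "The non-inferiority of the BM-MSCs group relative to the control group is evaluated based on whether the lower limit of the 95% CI exceeds" the 15% margin (taken here as a lower limit above −15 points). The only analysis set named anywhere is a full analysis set, under Ethics approval and current status. The section also refers to a statistical analysis plan, which is not shown.

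The order of events matters. Patients are randomised once eligibility is confirmed (Registration and informed consent). Table 1 puts marrow sampling after assignment and marks it for the BM-MSCs group only. Then, under Preparation and application of tissue engineered materials, "Autologous BM-MSCs are cultivated from the iliac crest bone marrow aspirate for about 6 to 8 weeks". The control group receives the same mixture without cells. The article does not say what a BM-MSCs patient receives if no cells are available, or how a segment with no transplant is scored.

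**The concern.** In a superiority trial, intention to treat usually works against a false claim when patients do not get their allocated treatment. In a non-inferiority trial that protection is lost, because anything that makes the arms more alike helps the claim. Here the opportunity for non-receipt is one-sided: a failed culture, or a withdrawal while waiting for one, can happen after randomisation in the BM-MSCs arm only. A patient in that arm treated without cells would have had exactly the control treatment and would still be counted as BM-MSCs.

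The arm is small, so few such patients are needed. It has at most 19 patients, and one of them is 1/19 = 5.3% of the arm, two are 10.5% and four are 21.1%. By segments, one patient can weigh more: the article reports 28 segments in the first 4 patients, an average of 7, and 7/55 = 12.7%. What is at stake is whether a reported non-inferiority, or a failure to show it, reflects the cells or the handling of patients who never received them.

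**Working it through.** **Inputs from the article.**
- Sites: "involving a total of 83 regions (BM-MSCs group: control group = 55 regions: 28 regions" (Overall design and objective).
- Success rates: "are commonly 95% in the two groups based on our clinical pilot study" (Sample size calculation).
- Margin: "The non-inferiority margin is set to be 15.0% as a clinically acceptable difference".
- Level: "two-sided significance level of 5.0"%, that is 2.5% one-sided for non-inferiority.

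**Assumed.** The share *f* of BM-MSCs segments that receive no cells, taken from 5% to 20%; what happens to those segments (cases A and B below); independent sites.

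**The plan's own figure first.** The Sample size section says: "With 83 sites per group, there was 80% power". Reading 83 as the total, as the design section does, the unpooled normal approximation gives

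SE = √[0.95 × 0.05 × (1/28 + 1/55)] = 0.0506; power = Φ(0.15/0.0506 − 1.96) = 84%.

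The same formula needs 25 + 50 = 75 sites for 80% power. A Farrington–Manning score calculation needs about 87 to 88 and gives 78% power at 55:28. So 83 in total lies between two standard methods without matching either; 83 per group would give over 99% power. That mismatch is a separate matter. The check below uses 55:28.

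**Method.** I enumerated all outcomes of two binomials (55 and 28) and added the probability of those where the lower 95% limit lies above −15 points. I used three rules for the limit: Wald, Newcombe and Farrington–Manning. The article names Clopper–Pearson, which is an interval for one proportion, so it does not by itself fix the rule for a difference.

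**Case A: patients without cells get the control mixture and succeed at 95%.** With cells truly at the margin (80% v 95%), the BM-MSCs rate under intention to treat is 0.80(1 − f) + 0.95f = 0.80 + 0.15f.

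| f | BM-MSCs rate | Wald | Newcombe | Farrington–Manning |
|---|---|---|---|---|
| 0 | 80.0% | 2.5% | 2.8% | 2.5% |
| 10% | 81.5% | 4.2% | 4.5% | 4.1% |
| 20% | 83.0% | 7.0% | 7.1% | 6.6% |

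The entries are the probability of a false non-inferiority claim.

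**Case B: patients without cells get no transplant and count as failures.** The rate is 0.80(1 − f) at the margin and 0.95(1 − f) under the planning assumption.

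| f | False claim, 80% v 95% (range over rules) | Power, 95% v 95% (range over rules) |
|---|---|---|
| 0 | 2.5–2.8% | 86–90% |
| 5% | 0.5–0.7% | 44–48% |
| 10% | 0.1–0.15% | 14–15% |

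**Mixtures of A and B.** Let *w* be the share of non-recipients who go untransplanted. Non-recipients succeed at 0.95(1 − w). Dilution raises the error only while this exceeds 0.80, that is while w < 1 − 0.80/0.95 = 15.8%. Above that, the bias turns against non-inferiority.

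**The case against.** Several points on the other side stand.

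- A reader might infer that intention to treat here necessarily favours a false claim. The article does not support that. It leaves the cells out of the mixture for the control group and says nothing of a BM-MSCs patient whose culture fails, so case A is an assumption. Withdrawal before surgery belongs to case B and does not dilute. At the planned 95% v 95%, case A changes nothing.
- The non-receipt fractions are assumed. Candidates with difficult marrow aspiration are excluded before randomisation, which closes part of one route; culture failure remains.
- Segments are clustered, at least three per patient, so the absolute error rates do not describe this trial. They show direction and rough size.
- A reader might also infer that the plan forbids any per-protocol analysis. The article is condensed, and the unseen analysis plan may contain one. What stands against the text is the word *All*: a supporting set in that plan would contradict the article's own sentence.
- A per-protocol set is not a clean comparator. Culture failure removes patients from one arm only, and if those patients have poorer marrow, the set flatters BM-MSCs. This weighs against making it co-primary, but not against a supporting analysis.
- The study calls itself exploratory and will weigh secondary endpoints. That limits the consequence, but the article still fixes a formal margin and decision rule.

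One objection fails: that inflation needs cells truly worse than control. That is the non-inferiority null hypothesis, under which the error rate is defined.

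**Conclusion.** The point holds in conditional form. The article commits all analyses of a non-inferiority trial to intention to treat, in a design where non-receipt of the test product can arise after randomisation in one arm only. The consequence depends on what happens to those patients. If they are treated with the control mixture, a nominal 2.5% error rises to somewhat over 4% at 10% non-receipt and about 7% at 20%. If they are left untransplanted and scored as failures, the false-claim risk falls below 1%, but at 5% non-receipt the power is roughly halved. A few patients could thus move the conclusion in either direction, and nothing named in the article would show which had happened. The sizes rest on independent sites, assumed non-receipt fractions and the two extreme cases. The documents do not support an unconditional bias toward non-inferiority, nor a need for a co-primary per-protocol test. This is a cheap improvement, not a fatal flaw.

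**What to change.** Amend the opening sentence of the Statistical analysis section so that:

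1. the primary non-inferiority analysis stays on the intention-to-treat (full analysis) set;
2. a pre-specified supporting per-protocol analysis is added, in patients randomised, transplanted with the allocated mixture and with an evaluable CT;
3. per-protocol membership is classified before CT results are reviewed by group, which matters because the trial is open-label;
4. non-inferiority is called robust only if the two analyses are consistent, and any disagreement is reported and explained;
5. the scoring of segments with no transplant under intention to treat is stated.

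What patients without cells receive is a clinical matter for the sponsor; no rule is proposed here.

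Cost: one extra analysis set, a few sentences and a slightly lower chance of a clean claim (not quantified here). The per-protocol set may itself be selected, since exclusions for culture failure can occur in one arm only; reporting the number and reason of exclusions by arm would let readers judge that.

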## Background

Maxillomandibular bone defects occur as a result of maxillofacial injury or surgery for maxillofacial tumors/cysts. Individuals with maxillomandibular bone defects may face limits in their daily living activities because of difficulty of eating without teeth, and unusual facial features; hence, it can have a major impact on the quality of life (QOL) of patients. While the standard therapy for these conditions is transplantation of autologous bone from the ilium, the tibia and any other bones, it is invasive for patients and hospitalization is necessary, further side effects such as infection and hematoma can arise [1]. In addition, bone grafts are occasionally absorbed at the implanted site depending on time [2, 3]. The other currently used therapy is the application of artificial bone (e.g. β-TCP, hydroxyapatite) at the defect area [4]; however, it is known that it takes a long time for ossification in cases of large defects and the implanted site often gets infected [5]. Another potential therapy is using a growth factor such as BMP-2 [6], but its efficacy has not been established in Japan and severe complications (e.g. edema in head and neck region) arise occasionally [7]. These treatments are still unsatisfactory; therefore, new regenerative therapies are required.

Meanwhile, bone regenerative cell therapy has been focused on in several experimental studies [8, 9]. We previously confirmed that transplantation of cultured BM-MSCs with PRP, thrombin, and calcium improved bone volume in non-clinical and clinical studies in patients with maxillomandibular bone defects or alveolar bone atrophy [10–19]; however, these clinical studies were a non-comparative single-arm design. Therefore, we planned a preliminary randomized controlled clinical study with the objective of confirming the efficacy of BM-MSCs in patients with maxillomandibular bone defects. In other words, we compare the efficacy and safety clinically of the mixture of “PRP, thrombin, calcium, β-TCP, and BM-MSCs” (BM-MSCs group), or the mixture of “PRP, thrombin, calcium, and β-TCP” (control group). We intend to add β-TCP as a prosthetic bone due to patients with larger defects in this clinical study than in previous clinical studies [10, 13–19].

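### Intention to treat is stated for every analysis, so patients assigned to cells but never transplanted stay in the denominator for post-transplantation adverse events

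*Protocol article*

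**What the plan says.** The Statistical analysis section sets one rule: "All the analysis is based on an intention to treat principle". It then describes the primary non-inferiority comparison and says that categorical variables are summarised by frequency and proportion. Safety is not excepted, and the section defers to a statistical analysis plan that is not shown.

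Safety falls within this rule. Under Overall design and objective: "The primary objective of this clinical study is to evaluate the efficacy and safety of bone regeneration therapy". The secondary endpoint list in Response variables (outcomes) ends with "Histological assessmentAdverse eventLaboratory tests" (three items run together in the text). That section adds: "In addition to achievement of the primary endpoint criteria, the clinical meaning of additional BM-MSCs in bone augmentation will be considered comprehensively according to these", where the last word points back to the outcomes in that list.

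On timing, Registration and informed consent describes enrolment "with subsequent randomized assignment to either the BM-MSCs group or control group by the minimization method". Preparation and application of tissue engineered materials then states: "Autologous BM-MSCs are cultivated from the iliac crest bone marrow aspirate for about 6 to 8 weeks". In Table 1 the early blood sampling and bone marrow sampling columns follow assignment and carry the footnote "Only BM-MSCs group". Adverse events are recorded from those columns onward.

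**The concern.** For efficacy, analysis as assigned protects the randomised comparison. For harm from a product, it mixes exposed and unexposed patients. Here the gap between assignment and exposure is long and falls mainly in one arm: a BM-MSCs patient must complete marrow collection and weeks of culture before receiving anything. If collection or culture fails, or the patient withdraws while waiting, there is no transplantation and so no event the mixture could have caused. The rule as written still counts that patient when the proportion with such events is calculated.

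The error makes the cell mixture look safer. The Background says that the programme under which the trial runs judges insurance coverage on efficacy and safety, so the reported harm rate has a use beyond the article. A per-protocol efficacy analysis would not help, because it leaves the adverse-event denominator unchanged.

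**Working it through.** The plan gives no figure on this point, so there is none to reproduce.

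**Inputs from the protocol article**
- Maximum patients: 19 BM-MSCs, 10 control (Overall design and objective).
- Assignment comes before marrow sampling and culture (Registration and informed consent; Table 1; Preparation and application of tissue engineered materials).
- The first patient registered in May 2016 and was transplanted in July 2016, arm not stated (Ethics approval and current status on this trial).

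**Assumptions, not in the document**
- k = number assigned to cells and never transplanted, taken as 0 to 4.
- p = rate of mixture-related events among transplanted BM-MSCs patients, taken as 10% to 50%.

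**Dilution of the BM-MSCs rate**

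As-assigned rate = p × (19 − k)/19.

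| k | multiplier | p = 10% | p = 20% | p = 30% | p = 50% |
|---|---|---|---|---|---|
| 0 | 1.000 | 10.0% | 20.0% | 30.0% | 50.0% |
| 1 | 0.947 | 9.5% | 18.9% | 28.4% | 47.4% |
| 2 | 0.895 | 8.9% | 17.9% | 26.8% | 44.7% |
| 3 | 0.842 | 8.4% | 16.8% | 25.3% | 42.1% |
| 4 | 0.789 | 7.9% | 15.8% | 23.7% | 39.5% |

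The relative reduction is k/19: about 5% for one patient and 21% for four.

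**No events observed**

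The exact one-sided 95% upper bound is 1 − 0.05^(1/n). It is 14.6% on n = 19 assigned, against 15.3% (n = 18), 16.2% (n = 17) and 17.1% (n = 16) on those transplanted.

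**Difference between arms**

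Take 30% with cells and 20% with the control mixture, again purely as assumptions, with all controls transplanted. The true excess is 10 points. As assigned it becomes 28.4 − 20 = 8.4, 26.8 − 20 = 6.8 or 25.3 − 20 = 5.3 points for k = 1, 2 or 3, a shift of 1.6 to 4.7 points. The standard error of the difference is √(0.30 × 0.70/19 + 0.20 × 0.80/10) = √(0.01105 + 0.01600) ≈ 0.164, so the 95% half-width is about 32 points.

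The shrinkage depends on non-receipt being mainly in the cell arm. If one of the 10 controls is also not transplanted, the control rate becomes 0.20 × 9/10 = 18.0%. With k = 1 the excess is then 28.4 − 18.0 = 10.4 points, not smaller than the true 10. The BM-MSCs rate itself is diluted in either case.

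**The case against.** **The analysis plan may define a safety set.** This is the strongest reply. Such a set is often left to that document, the Ethics section mentions a full analysis set, and an article condenses. A missing safety set is therefore no finding. But the article does more than leave it out: it states a rule for all analyses. A safety set in the analysis plan, or a full analysis set without untransplanted patients, would contradict that sentence, which would still need narrowing.

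**As-assigned reporting has value here.** It charges the cell strategy with the harms of marrow aspiration and additional sampling, even when no transplant follows. That stands. It is why the as-assigned table should be kept, and why the concern covers only events after transplantation.

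**The size is assumed and small.** Also true. No event rate or number of untransplanted patients is given, and a shift of 1.6 to 4.7 points is small beside a half-width of about 32. No safety hypothesis or decision rule depends on it.

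**Stronger readings that the document does not support**
- A reader might infer that laboratory summaries are diluted too. Post-operative laboratory visits are timed from the operation, so a patient never transplanted has no scheduled values to enter. Dilution would require a cell-arm patient to be given the control mixture, a route the article does not describe.
- A reader might infer that all blood collection is confined to the cell arm. The footnote covers the early sampling columns. Blood sampling on Day −1 carries no such mark, and both mixtures contain the patient's own PRP.
- A reader might take the Background remark that artificial bone "takes a long time for ossification in cases of large defects and the implanted site often gets infected" as evidence of an infection risk specific to cells. It concerns artificial bone, and β-TCP is in both mixtures.
- A reader might assume that every control patient reaches transplantation. The article does not say so.

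**Conclusion.** The point holds in a limited form. As written, the intention-to-treat sentence covers adverse events, and the design allows assignment to cells without transplantation. Following the rule would understate the rate of mixture-related events in the BM-MSCs arm by 1/19 (about 5% relative) for each untransplanted patient, if 19 are enrolled. The direction in that arm is certain whenever k is above zero and events have occurred. The effect on the difference from control also depends on how many controls go untransplanted.

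The size rests on assumed values of k and p, is zero if all are treated as assigned, and lies well inside the sampling error of 19 against 10 patients. The change is worth making because safety is a stated objective and the correction is almost free, not because a conclusion is shown to turn on it. The question is which patients form the analysis population; nothing in it touches clinical management.

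**What to change.** In Statistical analysis, replace the sentence with wording such as:

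> All efficacy analyses are based on the intention-to-treat principle. Adverse events from Day 0 onward are summarised per patient by the mixture actually received, among transplanted patients. All adverse events between assignment and Day 0, including those of blood and bone marrow collection and of the culture period, are summarised separately by assigned arm; collection events are also shown among patients who underwent collection. A full as-assigned adverse-event table is given as supplementary.

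For a patient never transplanted, there is no Day 0; the second summary should hold all events from assignment onward. If the analysis plan already defines a safety set, align this wording with it.

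The cost is a few sentences in the protocol and a matching entry in the analysis plan. No new data are needed: Table 1 already records sampling, transplantation and adverse events by visit. The downside is that a comparison by mixture received among transplanted patients is not strictly randomised, which is the reason to keep the as-assigned table beside it.
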